### Outcome

2.8

The primary outcomes will be the decline of RF_CSA,_ the MRC-SS and time-to-event (defined as all-cause mortality or unplanned readmission to the ICU due to invasive ventilation). The activities of daily living will be accessed by the motor item of the Functional Independence Measure (FIM^TM^). Secondary outcome includes the expression level of MSTN, ICU length of stay, length of hospital stay, duration of invasive/non-invasive mechanical ventilation. The outcomes will be measure as follow:

#### Measurement of RF_CSA_

2.8.1

We will measure the RF_CSA_ on days 1, 3, 5, 7, 10, and 14 by B mode ultrasonography, using a 12L-SC (8.0-13.0 MHz, 7cm) linear array (Venue 50, GE Healthcare) at the First Affiliated Hospital of Guangzhou University of Chinese Medicine. RF_CSA_ will be measured on days 18, 21, 24, 28 if the patient continues to stay in the ICU. Patients will be prone to a 30° upwards incline at the head, except where the clinical conditions dictate otherwise. An excess of gel will be applied to minimize distortion. The transducer should be placed perpendicularly along the superior aspect of the upper leg, two-thirds of the distance between the anterior superior iliac crest and the superior patellar border. RF_CSA_ will be taken as an average of 3 consecutive measurements within 10% of 1 another. (A larger RF_CSA_ indicates a larger muscle mass). The point of measurement will be marked on the skin, and the same limb and location will be measured at each time point.^[1,24]^

#### Assessment of MRC-SS

2.8.2

Peripheral muscle strength will be measured according to the Medical Research Council sum-score (MRC-SS), which will result in a range of 0 to 60. Higher scores indicate greater muscle strength. Three muscle groups of each extremity will be tested bilaterally: shoulder abductors, elbow flexors, wrist flexors, hip flexors, knee extensors, and ankle dorsiflexors. Muscle weakness will be defined as an MRC-SS less than 48.^[25–27]^ When the patient is in a condition in which the MRC-SS cannot be fully evaluated (eg, 1 or more limb amputations or fractures; the limb cannot move due to indwelling tubing), a mean MRC-SS of less than 4 is used to indicate muscle weakness.^[26]^

Muscle strength will be evaluated at the first awakening and at ICU discharge. The first awakening is defined as the first day when the participant is alert, has a Richmond sedation and agitation scale between -1 and 1 (the Richmond sedation and agitation scale score range from -5 to +4, and -1 to +1 is the ideal score range for full cooperation to the MRC-SS test), and is able to follow at least 3 of the De Jonghe 5-command criteria.^[27]^

#### Language

2.8.3

This study will include subjects who speak non-Mandarin (including dialects such as Cantonese, Hakka, and Chaoshan and so on). The research team will recruit clinicians who can use the above dialects proficiently to participate in the study. After professional training, these clinicians will be able to explain the research plan and the questionnaire to the subjects in detail. If it is still too difficult for the patient to understand and cooperate because of a language gap, the researcher will explain the relevant content to the patient with the help of the patient's next-of-kin.

#### Quality of life: FIM^TM^

2.8.4

We will measure physical function by the motor item of the FIM^TM^ at day 28, day 90, six months, and 1 year after the admission to the ICU. The FIM^TM^ is a widely applied scale of functional abilities in rehabilitation patients. This scale can be used to assess a patient's ability to independently perform 13 daily activities (e.g., dressing, toileting, ambulating).^[28,29]^ Higher FIM^TM^ total scores indicate that patients need more help with these activities (score range from 13–91). The change in the FIM^TM^ will then be documented for each participant as the assessment of functional improvement of sepsis survivors.

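### The FIM motor score is given a direction that contradicts its own description, and its change has no stated pre-treatment reference, so a functional gain could be misread or hidden

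*Protocol article*

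**What the plan says.** The Outcome section (2.8) states: "The activities of daily living will be accessed by the motor item of the Functional Independence Measure". Section 2.8.4 says that the instrument "is a widely applied scale of functional abilities in rehabilitation patients" and continues: "This scale can be used to assess a patient's ability to independently perform 13 daily activities". It then gives the direction: higher "total scores indicate that patients need more help with these activities", with a range of 13 to 91.

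The score is collected "at day 28, day 90, six months, and 1 year after the admission to the ICU". The follow-up section (2.8.7) gives the same four times. The list of data collected at screening in 2.8.6 contains no FIM. Section 2.8.4 adds that the change in the score "will then be documented for each participant as the assessment of functional improvement of sepsis survivors". It does not say from which value the change is taken.

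**The concern.** There are two separate problems in one short section.

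- **Direction.** A score of how independently a patient performs activities should rise as the need for help falls. The printed sentence says the opposite. An analyst who follows it would report recovery as decline, on an endpoint that serves one of the aims in the Abstract (activities of daily living).
- **Reference for change.** If improvement is judged by change, and the first available score comes after treatment has started, the starting value may already carry part of the treatment effect. Subtracting that value removes the early effect from the comparison.

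The study is meant to inform a later multicentre study, so a lost effect or a wrong sign on daily function could be carried forward.

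**Working it through.** **1. Direction: the statements side by side.**

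- Name (2.8): a measure of functional independence.
- Description (2.8.4): a scale of abilities that assesses the "ability to independently perform 13 daily activities".
- Direction (2.8.4): higher means more help needed.

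The first two imply that higher is better; the third says that higher is worse. The other two functional measures have higher as better: a larger rectus femoris area means more muscle (2.8.1), and a higher MRC sum-score means more strength (2.8.2). The FIM sentence is the odd one out.

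The range does not settle the matter. 13 / 13 = 1 and 91 / 13 = 7, so 13 to 91 fits 13 items scored 1 to 7, but item scoring is not printed and the range would be the same in either direction. The finding is therefore an internal contradiction of wording.

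**2. Timing.** Under 2.5.1, acupuncture is assessed within 24 hours in patients who meet inclusion criteria 1 to 5. It then runs through the ICU stay or, after ICU discharge, until a 14-day course is complete. Treatment thus starts well before day 28, the first FIM visit in the text. Whether it has also ended by day 28 depends on the patient, since 2.8.1 allows for ICU stays up to day 28.

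**3. What change from day 28 measures.** Let D(t) be the acupuncture mean minus the control mean at visit t, with higher meaning more independent. Then:

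Difference in change from day 28 to t = D(t) − D(28).

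The values below are assumed for illustration; the protocol gives no expected FIM scores. Both arms start at 25 before treatment, and day 28 is 60 versus 50, so D(28) = 10.

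| 1-year means | D(1 year) | Change from day 28 | Difference in change | Difference from common start of 25 |
|---|---|---|---|---|
| 75 vs 65 | 10 | 15 vs 15 | 0 | 50 − 40 = 10 |
| 80 vs 75 | 5 | 20 vs 25 | −5 | 55 − 50 = 5 |

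In the first row a constant advantage disappears. In the second the sign reverses although acupuncture is ahead at both visits. In general, the change contrast has the wrong sign whenever 0 < D(t) < D(28). If there is no early effect, D(28) = 0 and nothing is lost.

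**4. Effect of the printed direction.** In the first row both arms rise by 15 points. Read as printed, both would be recorded as needing more help at 1 year than at day 28, and the acupuncture arm would appear 10 points worse at each visit.

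**The case against.** Several points on the other side are sound.

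- **The day-28 baseline is not written down.** Section 2.8.4 names no reference, and the participant timeline (Table 2) is not shown, so an earlier FIM could be listed there. A reader might infer that change can only be taken from day 28. The documents do not go that far: two sections agree on four visits and the screening list has no FIM, which makes an earlier score unlikely but does not exclude it.
- **Day 28 is not post-treatment for everyone.** A patient still in the ICU may still be receiving acupuncture. What holds is that day 28 falls after treatment has started.
- **The two faults need not add up.** In the second row, a change difference of −5 read with the printed direction would favour acupuncture. A reader might infer that both errors push towards apparent harm; they can also offset each other.
- **Imputation is not a further harm.** It is tempting to say that a reversed scale inverts the worst- and best-case imputation in 2.11. That section runs both and asks whether they agree. Reversing the scale swaps the labels and leaves the pair of results unchanged.
- **No data are lost.** No recoding is described, so raw scores can still be read correctly and compared at each visit. Section 2.10 fixes no FIM model, which an article may leave to the analysis plan.
- **The groups are not randomised (2.7).** A day-28 difference may partly reflect who received acupuncture, and change from day 28 would remove stable differences of that kind. It would remove an early treatment effect with them, so adjustment for pre-treatment covariates is the better tool.

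These points limit the size of the finding. They do not resolve the contradiction in direction or supply a reference for the change.

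**Conclusion.** The point holds at moderate severity. The stated direction of the FIM contradicts the article's own name for and description of the scale; this needs no assumption and no outside source. If followed, it reverses the reading of every FIM result.

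The change-score part is conditional. It rests on the four visits in the text being the complete FIM schedule and on day 28 being taken as the starting point. Under those conditions, any effect present by day 28 is subtracted from the later comparison. With the assumed 10-point early advantage, the reported difference in change is 0 if the advantage persists and −5 if it halves. These figures show the mechanism and are not estimates for this trial.

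The severity is no higher because 2.8 names three primary outcomes and FIM is not one of them, FIM does not enter the sample size in 2.3, and comparison of correctly read scores at each visit would still capture an effect.

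**What to change.** - Correct the sentence in 2.8.4 so that higher FIM motor scores mean greater independence, and check that the EDC scoring agrees.
- Define the FIM outcome as the adjusted between-group difference in score at day 28, day 90, 6 months and 1 year. Treat day 28 as an outcome, not as a baseline.
- If Table 2 does list a FIM before treatment, name it in 2.8.4 as the reference for change.

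The cost is one corrected sentence, one scoring check and one sentence defining the outcome. No new visit or data collection is needed.

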#### Collecting clinical samples (blood): MSTN

2.8.5

Concentrations of MSTN will be analyzed in serum using a sandwich-type enzyme-linked immunosorbent assay kit. Samples will be taken on day 1, day 7 and day 14 (or the time of ICU discharge) of the ICU admission. The samples will be stored at -80 °C in the Biomedical Research Library at Ling-Nan Medical Research Center for the assay.

#### Collecting healthcare data within the ICU stay

2.8.6

During the screening period, the relevant subject information will be completed, and baseline demographic-related items will be collected. The SOFA score, the immediate acute physiology and chronic health evaluation II score (and SAPS score), the GCS score, body temperature, mechanical ventilation or not, the infection site, the pathogenic examination before the administration of antibiotics or use of vasoactive drugs, arterial blood gas analysis, blood routine, coagulation function, liver function, kidney function, heart function, infection index, urine pregnancy test (female subjects), and an electrocardiogram will be recorded during this period. The length of the first antibiotic use and whether the pathogen is sensitive to the antibiotic will be recorded after initiation.

For patients who survive and are discharged from the ICU - meeting all inclusion criteria (1 to 6) - the mechanical ventilation duration time, LOS, total hospital stay, sum sedative analgesic dose, statin dose, blood glucose level, insulin dosage, glucocorticoid dosage, protective constraints, and the duration of neuromuscular blockers will be additionally recorded.

Table 2 shows a general view of the data collecting and the time of acquisition for each item. We will manage all study data anonymously, and all CRFs will be labelled with a study number allocated to each individual participant. The CRF will be in both paper and electronic formats. The paper version of the CRF will be used for backup storage of data and for verification when needed. The daily management of data will be completed on the EDC system. And the details of bedside data collection are shown in Table 3.

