#### Electronic data capture (EDC) System

2.4.1

The Department of Critical Care Medicine at the First Affiliated Hospital of Guangzhou University of Traditional Chinese Medicine has already deployed a cloud-based EDC system (website: https://study.empoweredc.com/site/203). Each patient will be assessed within 24 hours after ICU admission, and patients who meet the sepsis diagnosis will be entered into the system. Peripheral serum will be collected prospectively at baseline and at subsequent time points and will be stored in the biological sample bank (Ling-Nan Medical Research Center) to test MSTN expression levels. Patients who meet the SIM diagnosis will be marked in the EDC according to the diagnostic criteria. Two intensivists will measure the RF_CSA_ of the sepsis patients at the measurement time point and will then enter the data into the EDC system; a consistency evaluation will be performed. One ICU specialist and 1 neurologist will evaluate the medical research council sum-score (MRC-SS) of the SIM patients.

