#### Inclusion criteria

2.4.3

(1)Age 18 to 85 years old;(2)Met the criteria of Sepsis 3.0^[20]^, which defines sepsis as infection + sequential (sepsis) organ failure assessment score (SOFA) ≥ 2 points within the first 24 hours;(3)First ICU admission and the patient should be expected to survive within the first 48 hours;(4)Informed consent was signed by the patient or their next to kin;(5)The RF_CSA_ decreased more than 9.24%^[21]^ after ICU admission;(6)Alive during the ICU stay.

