### Study groups

2.7

Since this study is a real-world study, the grouping of the study subjects was determined by the actual observations. Therefore, no randomization of groups was set in this study. The subjects will be as allocated into 2 arms.

Group 1: acupuncture group

When the participant meets the inclusion criteria (1 to 5), the acupuncturist will assess the conditions for patient treatment. Patients can enter this group and have acupuncture treatment if they do not have specific conditions (such as edema, coagulopathy, acupoints local skin and soft tissue infection, and rejection of acupuncture treatment) that are not suitable for acupuncture.

Group 2: control group

Patients who are not suitable for acupuncture or are not willing to receive acupuncture could enter this group. In addition to basic treatment, patients in this group will be prescribed exercises, such as early in-bed activities or wheelchair activities.

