### Recruitment

2.9

Ninety-eight subjects will be needed over the timeline of 2 years according to our sample size calculation. Within 24 hours of admission to the ICU, the patient will be screened against the inclusion criteria. The signing of an informed consent form for inclusion in the study will be performed once the patient or next-of-kin agrees to participate in the study. Data will be assessed only by the researchers, and all data will be kept confidential. Patient recruitment will begin in November 2019, and the expected completion date of the study is December 2022.

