### Statistical analysis

2.10

All available data will be analyzed descriptively. For continuous data, the normality test will be applied at the very beginning of the analysis. We will bewrite the results as the means, standard deviations, and 95% confidence intervals (CIs) for continuous data that conform to the normal distribution; medians, quartiles, and ranges for rank data and continuous data that do not fit the normal distribution; and percentages for discrete data.

The change in the RF_CSA_ from baseline will be analyzed by a generalized additive mixed model of repeated measures design. Analysis of the time-to-event outcome (at day 28, day 90, six months, and 1 year after the admission of ICU) will be conducted by applying Kaplan-Meier curves. Kaplan-Meier survival curves will be performed to describe the survival rate between the 2 groups, and the log-rank method will be used to compare the survival rates of the acupuncture group and control group. Multivariate Cox proportional hazard regression models will be used to analyze several constituents (such as acute physiology and chronic health evaluation-II, SOFA score, demographic and diagnostic data), adjust for covariates, and correct for confounding. Our team will use similar approach mentioned above to analyze secondary outcome measures when they can be expressed as time-to-event outcome dimensions. All regression analyses (generalized additive mixed models, log-rank analysis, multivariate Cox proportional hazard regression models) will include the same covariates as the primary analysis. If there are any measurable differences between the 2 study groups with regard to prognostic factors, a propensity score analysis will be applied to assess the sensitivity of the results to any treatment allocation biases. The propensity score will be set for the main outcome. After the 2 sets of data are analyzed according to the previous analysis, the patients will be matched with the propensity score, and then the main outcomes of the matched 2 groups will be compared again to see if there are any similarities or differences between the 2 groups before and after the match. If they are the same, the results are stable; however, a difference means that there are factors affecting the evaluation of the outcome before the match, and these factors will need to be explained.

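### Allocation-related covariates are described only at ICU screening, but the non-random group is settled on day 3 or later, so adjustment may rest on proxies and leave an unknown share of the confounding

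*Protocol article*

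**What the plan says.** **When covariates are recorded.** Section 2.8.6 states: "During the screening period, the relevant subject information will be completed, and baseline demographic-related items will be collected". Its list for that period includes SOFA, APACHE II, SAPS, GCS, mechanical ventilation (yes or no) and laboratory work: "arterial blood gas analysis, blood routine, coagulation function, liver function, kidney function, heart function, infection index". Edema does not appear. Section 2.9 dates screening: "Within 24 hours of admission to the ICU, the patient will be screened against the inclusion criteria". Section 2.4.1 agrees: "Each patient will be assessed within 24 hours after ICU admission".

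**When the group is settled.** Section 2.7 has no randomization. It says: "When the participant meets the inclusion criteria (1 to 5), the acupuncturist will assess the conditions for patient treatment". Patients with conditions such as edema, coagulopathy or local infection, and those who refuse, go to the control group. Criterion 5 (section 2.4.3) requires that the rectus femoris cross-sectional area (RF_CSA) has "decreased more than 9.24"% since ICU admission. Section 2.8.1 schedules the scans "on days 1, 3, 5, 7, 10, and 14 by B mode ultrasonography", with later ones for patients still in the ICU.

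**How the groups are compared.** Section 2.10 says: "Multivariate Cox proportional hazard regression models will be used to analyze several constituents". It gives APACHE II, SOFA, demographic and diagnostic data as examples, with the aim of correcting for confounding, and says that all regression analyses share the covariates of the primary analysis. Propensity matching follows as a sensitivity analysis if the groups differ on prognostic factors. No measurement day is given for any covariate, and the propensity variables are not listed.

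**The concern.** Covariate adjustment is this trial's only protection against confounding by indication. It works through variables that describe the patient when the group is chosen. Two patients with the same SOFA at admission may differ widely a week later: one is recovering and judged suitable for needling, while the other is edematous with deranged clotting and becomes a control. A model that holds only their admission scores treats them as alike, and the difference between them passes into the estimated effect of acupuncture.

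Because the regression models share covariates, this reaches both the time-to-event comparison and the RF_CSA model. A propensity score built on the same values would carry it into the matched comparison of the main outcomes. The direction is foreseeable: sicker patients on the entry day are steered to control, which favors acupuncture.

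This is more than a detail for the analysis plan. An analysis plan can choose among recorded values, but it cannot use values that were not collected. Laboratory results might be recovered from charts. A standardized edema assessment in both groups probably could not.

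**Working it through.** The plan gives no figure on this point, so there is none to reproduce. The check has two parts.

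**1. The time gap**

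- Covariates: within 24 hours of ICU admission, so day 1 (sections 2.4.1, 2.8.6, 2.9).
- Group entry: needs criterion 5, a fall from the first scan (sections 2.4.3, 2.7). Day 1 is the baseline scan, so the fall can first be seen on day 3, then on days 5, 7, 10 or 14 (section 2.8.1).
- Gap on these scans: 3 − 1 = 2 days at the shortest, 14 − 1 = 13 days at day 14.

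If the screening period was meant to run until criterion 5 is met, that contradicts the 24-hour window in section 2.9. The covariate day would then be undefined, and the same clarification would be needed.

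**2. What adjustment for a day-1 proxy leaves behind**

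Let C be severity on the entry day, B severity on day 1 and T the group. Assume that allocation depends on B only through C, that the outcome depends linearly on C, and that adjustment is linear. Write rho = corr(B, C) and r = corr(C, T), so that corr(B, T) = rho × r. The unadjusted bias is proportional to r. After adjustment for B it is proportional to (r − rho × rho × r)/(1 − rho² r²). The share left is therefore

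(1 − rho²)/(1 − r² rho²).

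Neither rho nor r is in the documents; both are assumed. For example, with rho = 0.5 and r = 0.3: (1 − 0.25)/(1 − 0.09 × 0.25) = 0.75/0.9775 = 0.77.

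| rho | Share left, r = 0.3 | Range for r = 0.2 to 0.5 | Simulation, logistic allocation |
|---|---|---|---|
| 0.3 | 0.92 | 0.91–0.93 | 0.93 |
| 0.5 | 0.77 | 0.76–0.80 | 0.78 |
| 0.7 | 0.53 | 0.52–0.58 | 0.56 |
| 0.8 | 0.38 | 0.37–0.43 | 0.40 |
| 0.9 | 0.20 | 0.20–0.24 | 0.22 |

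The simulation used 1,000,000 patients per row. At rho = 0.5, for example, the bias went from −0.825 unadjusted to −0.646 adjusted, and 0.646/0.825 = 0.78. The mean difference of about 0.83 implies r ≈ 0.83 × 0.5 = 0.41 for a balanced binary group, and the formula at r = 0.4 gives 0.92, 0.78, 0.55, 0.40 and 0.22, in agreement.

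More than half of the bias remains only if rho < √(0.5/(1 − 0.5 r²)), which is 0.71 at r = 0.2, 0.72 at r = 0.3 and 0.76 at r = 0.5.

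**The case against.** The strongest reply is that the schedule itself is not visible. Section 2.8.6 refers to Table 2 for the time of acquisition of each item and to Table 3 for bedside collection, and neither is shown. SOFA or coagulation may be repeated there. This stands as a limit on certainty. The prose of section 2.8.6 does give times for its items (screening, after antibiotics are started, and for survivors at ICU discharge), and none is group entry. But prose alone does not prove that nothing is repeated.

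Second, a reader might infer that the planned adjustment uses the wrong day's values. The documents do not say so. Section 2.10 offers an open list of covariates, fixes no day and does not name coagulation, which is recorded but not stated to be in any model. Covariate timing may also be settled in an analysis plan that is not shown.

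Third, a reader might infer that most of the confounding survives adjustment. That depends on a correlation that the documents do not give. With a gap as short as two days a high correlation is plausible, and at 0.8 or 0.9 well under half remains. The calculation also assumes linear adjustment, whereas the plan uses Cox models and matching.

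Fourth, group membership also follows the wishes of the patient or family (sections 2.5.1 and 2.7). No day's clinical values would remove that part.

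Finally, the whole-stay totals in section 2.8.6 (such as sedative, insulin and glucocorticoid doses) include time after treatment starts and would be poor covariates, but section 2.10 does not propose them, so nothing there needs correcting.

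What the reply does not answer is the gap itself: the text shown places the measures at admission and the allocation at least two days later.

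**Conclusion.** The point holds as a timing mismatch in the text shown. Severity, ventilation and coagulation are tied to the first 24 hours and edema is not listed, while the non-random group is settled 2 to 13 days later on the scans to day 14, partly on edema and coagulopathy. Admission values are then proxies for what drives allocation.

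The size is unknown. Under the assumptions above, adjustment for day-1 severity leaves about 92% of this component at a correlation of 0.3 and about 20% at 0.9. These are shares of the part of confounding that runs through entry-day severity, not of all confounding, and they say nothing about the absolute bias. The conclusion rests on the prose of sections 2.4.1, 2.7, 2.8.1, 2.8.6, 2.9 and 2.10. It would weaken if Table 2 or 3 schedules a repeat at group entry.

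This is a cheap and worthwhile correction to a declared pilot. It does not show that the planned analysis is invalid.

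**What to change.** - **Section 2.8.6 (and Table 2, if it does not already provide for this):** record SOFA, coagulation results, edema, and ventilation and vasopressor status in both groups when criteria 1 to 5 are met and before the group is determined.
- **Section 2.10:** state that these entry values, together with the RF_CSA at qualification and the ICU day of qualification, enter the Cox, mixed and propensity models. The last two are already available from the dated scans.
- **Sections 2.8.6 and 2.9:** say whether the screening period ends at 24 hours or runs until criterion 5 is met.
- **Reporting:** acknowledge that selection by patient or family willingness remains after this change.

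The cost is about one extra page in the electronic data capture system per patient, or about 98 pages at the planned enrollment. Most of it is routine ICU chart data; a standardized edema assessment is the main new item.
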